### Tuina Therapy

The most commonly used methods for the treatment of NNP were loosening tendons, pulling tendons, and smoothing tendons. The treatment was performed 3 times a week for a total of 4 weeks. The operation time and key points of each technique are shown in Table 1.

**Table 1. T1:** Detailed manipulation of Tuina therapy used in the intervention group for patients with nonspecific neck pain in this randomized controlled trial.

Technique name	Frequency	Key points
Loosening tendons	100 times/min, 5 min	Put the thumb and index finger pulp on the muscles on both sides of the cervical spine, from top to bottom, and massage the neck and shoulder muscles circularly.
Pulling tendons	80 times/min, 5 min	The thumb pulp focuses on one side of the neck and shoulder muscles, and the 2 sides are moved alternately.
Smoothing tendons	80 times/min, 5 min	Put the pulp of the thumb and index fingers of both hands under the occipital posterior tuberosity of the neck and push and smooth the neck muscles from top to bottom.

The 3 manipulations are applied with distinct depth and force characteristics:

Loosening tendons: targets the superficial muscles and subcutaneous tissue, applied with light-to-moderate pressure (approximately 5‐15 N).Pulling tendons: reaches the intermediate to deep muscle belly and myofascial attachments, applied with moderate-to-firm pressure (approximately 10‐25 N).Smoothing tendons: acts on the superficial to intermediate muscle layers, applied with light-to-moderate pressure (approximately 5‐15 N).

The force ranges are based on published biomechanical data on cervical Tuina. The end point of force application is the patient’s subjective sensation of soreness and distension (deqi-like sensation) without sharp pain. Each session lasts approximately 20 to 30 minutes, including brief rest intervals between techniques.

### Extracorporeal Shock Wave Therapy

ESWT will be performed using a Swiss Storz extracorporeal shock wave therapeutic apparatus (MP50). The MP50 device delivers radial (dispersive) shock waves, characterized by a divergent wave pattern that distributes energy over a broader, more superficial tissue area. Each session will deliver 2000 shocks at a pressure of 1.5 to 2.0 bar and a frequency of 10 to 12 Hz, with moderate handle pressure. Based on the pressure range and radial wave characteristics, the estimated energy flux density ranges from 0.10 to 0.20 mJ/mm², which falls within the medium-energy category as defined by international consensus guidelines (medium estimated energy flux density: 0.08‐0.28 mJ/mm²). The therapy will target tender points and the surrounding soft tissues. Treatment will be administered on days 1, 5, 10, 15, 20, 25, and 30.

### Outcomes

#### Overview

The primary outcome measure will be the VAS. Secondary outcome measures will include the Neck Disability Index (NDI), cervical active range of motion (AROM), shear wave elastography (SWE) using musculoskeletal ultrasound, and serum inflammatory factors. The assessment schedule is as follows: all outcome measures will be evaluated at baseline, during treatment (2 and 4 wk), and at the 8-week follow-up, except for SWE and inflammatory factors. SWE will be measured at baseline, 4 weeks, and follow-up; inflammatory factors will be measured at baseline and 4 weeks.

#### Primary Outcome Measurement

The VAS is a commonly used instrument for pain assessment, designed to enable patients to quantify their pain intensity using a simple linear scale. A 10-centimeter scale will be employed, with end points labeled “0” (no pain) and “10” (the most severe pain imaginable). Patients will indicate the point on the scale that reflects their current pain experience. The primary efficacy end point is the change in VAS score from baseline to the end of the 4-week treatment period. The VAS is primarily utilized to evaluate pain intensity; it may also serve to compare treatment outcomes and to monitor changes in emotional and functional status.

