### Monitoring and Quality Control

#### Overview

A formal independent data monitoring committee will not be established because both Tuina and ESWT are noninvasive, low-risk interventions with well-established safety profiles, and no interim efficacy or futility analyses are planned. Instead, the PI will assume responsibility for safety monitoring. The PI will review AE data weekly and submit periodic safety summaries to the institutional ethics committee. All SAEs will be reported to the ethics committee within 24 hours of the investigator becoming aware of the event.

As ESWT may cause transient procedural pain or discomfort, participants in the ESWT group will be asked to rate their pain during treatment using VAS after each session. A score ≥7 or any persistent discomfort lasting beyond the treatment session will trigger a review by the PI. If necessary, ESWT parameters (pressure and frequency) will be adjusted, or the session will be terminated early.

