#### Primary Outcome Analysis

The primary end point is the change from baseline in the VAS score at week 4. The primary analysis will use a mixed-effects model for repeated measures (MMRM) with VAS at weeks 2, 4, and 8 as dependent variables. The model will include the treatment group, time, and their interaction as fixed effects and baseline VAS as a covariate; an unstructured covariance matrix will model within-subject correlations. From this model, the estimated difference between Tuina and ESWT at week 4 will be derived, along with its 95% CI. MMRM inherently accommodates missing data under the missing-at-random assumption. Multiple imputation will be used as a sensitivity analysis to check robustness.

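### The primary pain score is a momentary rating at week 4, but the two treatment calendars end on different days, so time since the last session is not comparable between arms

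*Protocol article*

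**What the plan says.** Under Primary Outcome Measurement, the Protocol article defines the VAS as a rating of pain at the moment of asking: "Patients will indicate the point on the scale that reflects their current pain experience". The same section sets the time point: "The primary efficacy end point is the change in VAS score from baseline to the end of the 4-week treatment period". The Overview under Outcomes gives the schedule: "all outcome measures will be evaluated at baseline, during treatment (2 and 4 wk), and at the 8-week follow-up". Primary Outcome Analysis uses a "mixed-effects model for repeated measures (MMRM) with VAS at weeks 2, 4, and 8 as dependent variables" and takes the treatment difference at week 4.

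The treatment calendars are stated separately. For ESWT: "Treatment will be administered on days 1, 5, 10, 15, 20, 25, and 30". For Tuina: "The treatment was performed 3 times a week for a total of 4 weeks"; weekdays are not given. Exercise Therapy and Self-Stretching adds exercise at every treatment visit in both arms.

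On short-lived sensations, the Overview under Monitoring and Quality Control begins "As ESWT may cause transient procedural pain or discomfort". It then has ESWT participants alone rate pain after each session and sends discomfort that outlasts the session to the principal investigator for review. The Tuina Therapy section says: "The end point of force application is the patient’s subjective sensation of soreness and distension", with the qualification that there should be no sharp pain.

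Baseline is assessed before the allocation envelope is opened (Randomization and Allocation Concealment). The text at hand does not say whether the week-2 and week-4 VAS come before or after a session, or how long after one. Figure 3, the schedule, is not shown in the copy reviewed.

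**The concern.** A rating of current pain picks up whatever the participant feels at that moment, including soreness or relief from a recent session. That is harmless to the comparison if both arms are rated at the same distance from treatment. Here the two calendars have different spacing and different last days, and the ESWT calendar extends past the 4-week period that defines the primary end point. The interval from last session to rating, and the share of the course received by then, can therefore differ by arm because of the design itself.

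The analysis cannot repair this. Baseline VAS precedes any trial treatment, so adjusting for it removes nothing that arises later. The MMRM estimates the week-4 difference in the scores as recorded, including any transient component.

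**Working it through.** **1. The plan's own figure.** Sample Size Calculation uses a difference of 1.5 points and SD 1.8, so d = 1.5/1.8 = 0.83. A two-sided two-sample t test at 0.05 with 24 per group has power 80.7% by the noncentral t distribution (the protocol gives 81.2%). With 15% dropout, 24/0.85 = 28.2, rounded up to 29 per group and 58 in total. The sample size reproduces, and the point does not depend on it.

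**2. The ESWT calendar against possible VAS days.** Sessions are on days 1, 5, 10, 15, 20, 25 and 30.

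| VAS day | Days since last ESWT session | Days to next | ESWT sessions given |
|---|---|---|---|
| 14 | 14 − 10 = 4 | 1 | 3 of 7 |
| 15, before session | 15 − 10 = 5 | 0 | 3 of 7 |
| 15, after session | 0 | 5 | 4 of 7 |
| 28 | 28 − 25 = 3 | 2 | 6 of 7 |
| 29 | 29 − 25 = 4 | 1 | 6 of 7 |
| 30, before session | 30 − 25 = 5 | 0 | 6 of 7 |
| 30, after session | 0 | none | 7 of 7 |

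**3. The Tuina calendar.** Three sessions a week for 4 weeks make 12. If week 1 starts on day 1, the last falls on or before day 28.

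- *Week 4 read as day 28:* ESWT is rated 3 days after a session with 6 of 7 given. Tuina may have 12 of 12 given, the last on the same day or within a few days. The intervals match only if the last Tuina session happens to fall on day 25.
- *Week 4 read as the end of ESWT:* the rating falls on day 30, a session day, or later. On day 30 the last Tuina session is at least 30 − 28 = 2 days past.

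Under neither reading does the stated schedule make the arms comparable in time since treatment.

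**4. What an imbalance would do (assumed values only).** The documents give no size for residual soreness. Let b be the net extra VAS points in one arm at week 4, with SD 1.8 and the t test above. The noncentrality is (difference/1.8) × √(n/2). The third and fourth columns put b in the ESWT arm with no true difference, so the difference is b. The last column puts b in the Tuina arm against a true 1.5-point Tuina benefit, so the difference is 1.5 − b.

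| b | b/1.5 | Rejection, n = 24 per group | Rejection, n = 29 per group | Power, n = 24 per group |
|---|---|---|---|---|
| 0 | 0% | 5.0% | 5.0% | 80.7% |
| 0.25 | 17% | 7.6% | 8.2% | 65.4% |
| 0.50 | 33% | 15.6% | 18.0% | 47.0% |
| 0.75 | 50% | 29.3% | 34.5% | 29.3% |
| 1.00 | 67% | 47.0% | 54.8% | 15.6% |

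**The case against.** The strongest reply is that this is visit-level detail. Whether a scale is filled in before or after a session belongs in the schedule, the case report form or the full protocol. The article is a condensed document, its schedule figure was not available, and it says assessors are trained to collect outcomes in a standard way. That stands as far as it goes: the silence on order alone would not be a finding. It does not answer the calendar. A 4-week treatment period and a day-30 session are both stated in the text, and a visit window would not by itself reconcile them.

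Three stronger readings are tempting, and the documents do not support them.

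- *That ESWT pain contaminates the week-4 score.* The protocol says only that ESWT may cause transient pain, and it treats discomfort beyond the session as an event for review. At day 28 the last ESWT session is 3 days past, and a day-30 session cannot affect an earlier rating. Same-day overlap needs a day-30 reading, or day 15 for week 2, and the text states neither.
- *That the bias favours Tuina.* Tuina force is itself guided by soreness and distension, and either treatment may bring brief relief. The net direction is unknown.
- *That procedural and efficacy VAS scores may be mixed up.* This is speculation. The procedural rating is taken in the ESWT arm only, for safety, while outcome assessors are blinded and take no part in treatment.

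It can also be said that week 8 is a check. Read as day 56, it lies 56 − 30 = 26 days after the last ESWT session. That is useful, but it is not the primary time point.

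**Conclusion.** The point holds in a limited form. The primary outcome is a momentary rating. The stated calendars leave its distance from treatment, and the share of treatment received, unequal or undetermined between arms under either reading of week 4. Short-lived treatment effects may therefore enter the primary contrast to different extents. The text does not show that they do, in which direction, or by how much.

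The illustration of 0.25 to 0.75 points, or 17% to 50% of the planning difference, rests wholly on assumed values and on the imbalance not being offset by the other arm. It shows that a modest imbalance would matter at this sample size; it is not an estimate. What is firm is that the 4-week period and the day-30 session do not agree. The change is worth making because the source of bias is avoidable and cheap to remove.

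**What to change.** 1. Reconcile the 4-week treatment period (Study Design, Interventions, Primary Outcome Measurement) with the day-30 session (Extracorporeal Shock Wave Therapy). Which of the two is right is for the investigators. This must come first: a rating taken before the session on day 30 would still precede the last ESWT session.
2. Fix the day of the week-4 assessment relative to both treatment calendars.
3. State in the Outcomes Overview and Primary Outcome Measurement that the week-2 and week-4 VAS, and AROM and SWE where scheduled, are taken before any Tuina, ESWT or exercise that day, with the same minimum interval since the last session in both arms.
4. Record the date and time of the last session at each assessment.

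The cost is wording in the protocol and case report form, and slightly tighter visit scheduling. By 30 March 2026, 26 of 58 participants had been enrolled, leaving 58 − 26 = 32 still to be enrolled at that date. Those already enrolled may have been assessed under looser timing; where session and assessment dates exist, the interval can be worked out and its balance between arms reported.

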#### Secondary Outcome Measurements

##### Neck Disability Index

The NDI consists of 10 items evaluating 2 domains: neck pain and associated symptoms (pain intensity, headache, concentration, and sleep) and activities of daily living (personal care, lifting, reading, work, driving, and recreation). Each item is rated on a 0 to 5 scale, yielding a maximum total score of 50. The total score is expressed as a percentage, with 0% representing no disability and 100% representing complete disability; higher scores reflect more severe functional impairment.

##### Active Range of Motion

Cervical AROM will be assessed using a goniometer, evaluating 6 directions: flexion, extension, left and right lateral flexion, and left and right rotation. During measurement, the patient will be seated in a relaxed posture with the head and neck in a neutral position. The patient will be asked to actively perform each movement 3 times, and the average value will be used for analysis. Normal reference values for cervical AROM are 30° to 45° for flexion, 30° to 45° for lateral flexion, and 60° to 80° for rotation.

##### Shear Wave Elastography

SWE will be performed using a high-end color Doppler ultrasound system equipped with SWE functionality, using a high-frequency linear array transducer (frequency range: 4‐18 MHz). For the sternocleidomastoid muscle, the patient will be placed in the supine position with the head rotated slightly to the contralateral side to expose the muscle belly. For the upper trapezius muscle, the patient will be seated in an upright position with the head in neutral alignment and arms relaxed at the sides. Both measurements will be performed with the patient instructed to remain relaxed and avoid voluntary muscle contraction. Conventional B-mode ultrasound will be performed first to localize the bilateral sternocleidomastoid muscles and the upper trapezius muscles. The system will be switched to the SWE mode. The transducer will be placed gently on the skin surface (without compression), and stable elastographic images will be acquired along the longitudinal axis of the muscle fibers. After the image stabilizes for 5 seconds, the region of interest will be placed in the central portion of the muscle belly, avoiding blood vessels and bone. Shear wave velocity (m/s) will be measured. Three repeated measurements will be performed at each site, and the mean value will be used for statistical analysis.

##### Serum Inflammatory Factors

Before and after treatment, 4 mL of venous blood will be collected from each patient using a separating gel tube. The collection will be performed by a professional nurse from the Rehabilitation Medical Center of the General Hospital of Ningxia Medical University. Blood samples will be allowed to stand at room temperature for 20 minutes, followed by centrifugation at 3500 rpm for 10 minutes. The upper serum layer will be separated and stored in a refrigerator at −80 °C. Serum levels of stromal cell–derived factor-1, C-X-C chemokine receptor type 4, NOD-like receptor protein 3, interleukin-1β, interleukin-8, interleukin-6, and tumor necrosis factor-α will be measured using enzyme-linked immunosorbent assay.

### Efficacy Evaluation Criteria

The efficacy of the intervention will be evaluated using the improvement rates of the VAS for pain intensity and the NDI for functional status. The percentage improvement for both measures will be calculated as (baseline score−posttreatment score)/baseline score×100%. Clinical response will be classified into 3 categories based on simultaneous satisfaction of both criteria: markedly effective (VAS improvement ≥50% and NDI improvement ≥50%), effective (VAS improvement ≥30% and <50%, NDI improvement ≥30% and <50%), and ineffective (VAS improvement <30% and NDI improvement <30%). If a patient meets different classification levels across the 2 measures, the lower classification will be assigned. The overall clinical effective rate will be calculated as (number of markedly effective cases+number of effective cases)/total number of eligible cases×100%. The threshold of 30% improvement represents the minimum clinically important difference established for both VAS and NDI in patients with neck pain, while the 50% threshold represents substantial clinical benefits, indicating a truly successful outcome [23-25].

### Data Collection and Management

Data will be collected using printed case report forms and entered into an electronic case report form by independent researchers in a timely manner. Paper case report forms will be stored in a locked cabinet in the researcher’s office, and the electronic dataset will be deidentified and locked. Access to these records will be limited to authorized data administrators and statisticians. All study documents will be retained for at least 5 years after publication.

Following the ITT principle, all randomized participants will be included in the final analysis. For participants who discontinue the intervention or deviate from the protocol, primary and secondary outcome data will still be collected at scheduled time points whenever possible, AEs will be continuously monitored, and detailed reasons for discontinuation or deviation will be documented.

### Monitoring and Quality Control

#### Overview

A formal independent data monitoring committee will not be established because both Tuina and ESWT are noninvasive, low-risk interventions with well-established safety profiles, and no interim efficacy or futility analyses are planned. Instead, the PI will assume responsibility for safety monitoring. The PI will review AE data weekly and submit periodic safety summaries to the institutional ethics committee. All SAEs will be reported to the ethics committee within 24 hours of the investigator becoming aware of the event.

As ESWT may cause transient procedural pain or discomfort, participants in the ESWT group will be asked to rate their pain during treatment using VAS after each session. A score ≥7 or any persistent discomfort lasting beyond the treatment session will trigger a review by the PI. If necessary, ESWT parameters (pressure and frequency) will be adjusted, or the session will be terminated early.

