All interventions will be performed by qualified practitioners. Tuina manipulations will be delivered by practitioners holding a Physician Qualification Certificate and a Physician Practice License in Traditional Chinese Medicine, Acupuncture-Tuina, or Rehabilitation Medicine, with at least 3 years of clinical experience in Tuina. ESWT will be administered by practitioners holding a Physician Qualification Certificate and a Physician Practice License or a nationally recognized rehabilitation therapist certificate, who have completed specialized shock wave training and possess at least 1 year of clinical experience in shock wave therapy. Prior to study initiation, all intervention providers will undergo standardized training on the study protocol and pass a competency assessment. Ongoing quality monitoring will be conducted quarterly throughout the study.

Patients can choose to withdraw from the study at any time. Any significant improvement or deterioration in the condition of a participant, including adverse events (AEs), will be monitored throughout the trial. AEs will be reported to the principal investigator (PI), who will monitor the affected participants and investigate the potential causes.

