#### Individual Participant Stopping Rules

The study intervention will be discontinued for an individual participant if (1) the participant withdraws consent, (2) an SAE occurs that is assessed as probably or definitely related to the intervention, (3) the participant experiences intolerable procedure-related pain (ESWT-related pain score ≥7 on 2 consecutive sessions despite parameter adjustment), or (4) the PI determines that continuation poses an unacceptable risk to the participant. Discontinued participants will continue to be followed up for outcome assessment according to the ITT principle.

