### Data Analysis

#### Analysis Populations

Three populations will be defined: the ITT population (all randomized, primary analysis), the per-protocol population (≥80% sessions completed and primary outcome assessed, sensitivity analysis), and the safety population (≥1 intervention received, safety analyses).

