#### Baseline and Safety Comparisons

Baseline characteristics will be summarized by the group using descriptive statistics. Continuous variables will be compared using the independent *t* test or Mann-Whitney *U* test as appropriate; categorical variables with the chi-square test or Fisher exact test. Safety end points will be presented descriptively.

All analyses will use 2-tailed tests, and the primary outcome will be tested at *α*=.05. Analyses will be performed using IBM SPSS 26.0 and GraphPad Prism 9.0.

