This trial has several methodological limitations that should be acknowledged. First, owing to the nature of the interventions, participants and therapists cannot be blinded; this may introduce performance and expectation biases, which we have sought to mitigate through blinded outcome assessment, standardized information on treatment credibility, and analysis of blinding integrity. Second, the treatment session frequency differs between groups (12 Tuina sessions vs 7 ESWT sessions). This discrepancy reflects real-world clinical practice but could confound the estimated treatment effect; we plan to examine the influence of session attendance in sensitivity analyses and discuss it as a potential limitation. Third, the sample size (58 participants) was calculated to detect a large effect size; if the true between-group difference is smaller, the trial may be underpowered. Accordingly, treatment effect estimates and CIs will be emphasized over binary significance statements. Fourth, this is a single-center study, which may limit generalizability; a future multicenter trial would enhance external validity. Fifth, the 4-week follow-up period is relatively short and may not capture the long-term sustainability of treatment effects.

The findings of this trial are expected to provide comparative data that may inform clinical decision-making for individuals with NNP. If Tuina proves superior to ESWT in reducing pain and disability, its advantages of low equipment requirements and patient comfort could support its adoption as a preferred nonpharmacological treatment, particularly in settings with limited access to shock wave devices. Conversely, if Tuina does not demonstrate superiority, ESWT would retain its role as an evidence-based physical modality, while Tuina might still be considered a viable alternative, given its practical advantages, provided that its clinical effects are comparable. Regardless of the outcome, the trial will generate evidence on the differential effects of these 2 interventions on pain, function, muscle elasticity, and inflammatory biomarkers, contributing to more individualized treatment selection.

In conclusion, this protocol describes a methodologically rigorous randomized trial designed to address a specific evidence gap. The results, interpreted within the context of the acknowledged limitations, will contribute to the evidence base for nonpharmacological management of NNP.

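### Procedural pain is asked about after every session in the ESWT arm only, so tolerability cannot be compared fairly between arms and the patient-comfort advantage named for Tuina has no comparative data behind it

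*Protocol article*

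**What the plan says.** All references are to the protocol article.

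- **ESWT arm.** Monitoring and Quality Control (Overview): "participants in the ESWT group will be asked to rate their pain during treatment using VAS after each session". The rating has a defined use: "A score ≥7 or any persistent discomfort lasting beyond the treatment session will trigger a review by the PI". Individual Participant Stopping Rules uses the same score again: "ESWT-related pain score ≥7 on 2 consecutive sessions despite parameter adjustment".
- **Tuina arm.** No section describes a per-session rating. Tuina Therapy defines the end point of force as the patient's "subjective sensation of soreness and distension (deqi-like sensation) without sharp pain".
- **Both arms.** Interventions provides general surveillance: "Any significant improvement or deterioration in the condition of a participant, including adverse events (AEs), will be monitored throughout the trial". The principal investigator reviews adverse-event data weekly. A log is signed by participant and practitioner at each session.
- **Analysis.** Baseline and Safety Comparisons: "Safety end points will be presented descriptively".
- **Interpretation.** The Discussion says of Tuina, on condition that it proves superior on pain and disability, that "its advantages of low equipment requirements and patient comfort could support its adoption as a preferred nonpharmacological treatment". Its five listed limitations include the differing number of sessions (12 and 7) but not the differing way in which discomfort is collected.

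**The concern.** Asking a participant about pain at a fixed time usually brings out more reports than waiting for the participant to mention it. If one arm is asked after every session and the other is not, a difference in recorded discomfort mixes a difference between treatments with a difference in how hard one looked.

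Discomfort in the unasked arm is foreseeable on the protocol's own terms. Tuina is applied to the point of soreness, one of its three techniques uses moderate-to-firm pressure, and it has more sessions.

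What is at stake is the tolerability picture in a head-to-head trial whose authors already name comfort as a reason why Tuina might be preferred. None of the listed outcomes measures comfort in both arms. The only session-level discomfort data described come from one arm.

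**Working it through.** **1. Planned ratings.** Inputs: 29 per group (Sample Size Calculation); Tuina 3 per week × 4 weeks = 12 sessions (Tuina Therapy); ESWT on days 1, 5, 10, 15, 20, 25 and 30 = 7 sessions (Extracorporeal Shock Wave Therapy). Both session counts agree with the Abstract and the Discussion.

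- ESWT: 29 × 7 = 203 solicited ratings at full attendance.
- Tuina: 0 solicited ratings over 29 × 12 = 348 sessions.

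These figures count opportunities to record discomfort. They do not measure bias.

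**2. Illustration with equal risk per participant.** The documents give neither the risk of reportable procedural discomfort nor the share that general monitoring would pick up, so both are assumptions here. Let the true risk per participant be p in both arms, with full capture in ESWT and a capture fraction s in Tuina. The apparent excess in ESWT is p − ps = p(1 − s).

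- p = 10%, s = 50%: 10% − 5% = 5 percentage points.
- p = 30%, s = 10% to 50%: 30% against 3% to 15%, that is 29 × 0.30 = 8.7 participants against about 0.9 to 4.3.
- p = 50%, s = 10%: 50% − 5% = 45 percentage points.

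Over p from 10% to 50% and s from 10% to 50%, a true difference of zero appears as 5 to 45 points against ESWT.

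**3. Illustration with equal risk per session.** Let the true risk per session be q in both arms, independent between sessions (again assumptions). The proportion of participants with at least one recorded event is 1 − (1 − q)^7 in ESWT and 1 − (1 − qs)^12 in Tuina. The true Tuina figure is 1 − (1 − q)^12.

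| q | ESWT, recorded | Tuina, true | Tuina, recorded (s = 10% to 50%) |
|---|---|---|---|
| 2% | 13.2% | 21.5% | 2.4% to 11.4% |
| 5% | 30.2% | 46.0% | 5.8% to 26.2% |
| 10% | 52.2% | 71.8% | 11.4% to 46.0% |

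In every row Tuina has the higher true risk per participant, because it has more sessions, yet the lower recorded one. At q = 5% the order reverses whenever s is below [1 − 0.95^(7/12)]/0.05 = 0.0295/0.05, or about 59%. Above that, the order is right but the gap is understated unless capture is complete.

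**4. Reach of the problem.** The distortion applies to procedural pain and mild discomfort. Serious events would usually surface whether or not anyone asks, so the effect there is likely weak. The primary VAS is collected on the same schedule in both arms, and nothing above bears on it.

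**The case against.** The strongest reply is that the rating is a safety device for a known effect of ESWT. Its stated uses are review by the principal investigator, adjustment of the device and the stopping rule. It is neither an outcome nor part of any described analysis, and the article does not say that a score counts as an adverse event or will be compared between arms. Adverse events are monitored in both arms, Tuina participants have more contacts at which to report, and the wording of adverse-event questions is a detail that an article may leave to the full protocol or case report form. The comfort remark is conditional, hedged Discussion text.

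Most of this stands, and it limits the point. It does not remove it. The ESWT-only rating is a stated procedure, not an omitted detail. Descriptive tables suffer from unequal ascertainment as tests do. The article nowhere keeps these scores, or events found through them, out of the safety summary. However hedged, the comfort remark is a comparative claim without comparative data.

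A reader might infer more than the documents support:

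- *That ESWT must look worse whatever the truth.* Solicited reports typically exceed unsolicited ones, but not always. At q = 5% and s = 50% the recorded gap is only 30.2% against 26.2%.
- *That repeated VAS ratings anchor the primary outcome.* This is speculation. The session rating asks about pain during treatment and the outcome VAS about current pain, and neither a direction nor a size of bias can be derived.
- *That the ESWT-only file unblinds the analysts.* Nothing places it in the primary dataset. Attendance data, with 12 sessions against 7, could already reveal which coded group is which.

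**Conclusion.** The asymmetry is real, and it is not listed as a limitation. Solicited ratings number up to 203 in one arm and none over 348 sessions in the other, so any descriptive comparison of procedural pain or tolerability would tend to favour Tuina. The trial as described cannot support a comfort advantage for it.

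The counts rest on full attendance. The size of the distortion cannot be fixed from the documents: under the equal-risk assumptions in the first illustration it runs from 5 to 45 percentage points, and with equal risk per session the order of the arms can reverse. The direction rests on general monitoring capturing less than a direct question does.

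Serious adverse events are likely little affected, and no effect on the primary VAS estimate is shown. This is a worthwhile, inexpensive improvement to the safety data, not a threat to the primary analysis.

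**What to change.** **Preferred.** Add two items, identical in both arms, to the log already signed at each session: a post-session discomfort rating and one fixed adverse-event question. Keep them separate from the outcome VAS form. Summarise them per participant (worst rating, any event) and per session, because session numbers differ. State in the report that Tuina participants treated before the change have no ratings.

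**If this is not adopted.** Keep the ESWT-only scores, and adverse events identified solely through them, out of the between-arm safety summary and report them separately. Remove the patient-comfort statement from the Discussion, and list the unequal ascertainment among the limitations.

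Either way, the ESWT review trigger and stopping rule stay as they are; no view is taken on them.

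**Cost.** The preferred change needs a protocol amendment, which under Study Design means ethics approval, a registry update and notice to staff if it is treated as important. It adds an estimated minute per Tuina session, at most 348 minutes or about 5.8 hours over the trial. Tuina data will be incomplete: 26 of 58 participants were enrolled by March 30, 2026, so at most 58 − 26 = 32 participants, about 16 of them in the Tuina arm, could be covered from their first session had the change been made then. The fallback costs a few sentences.
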